   2. **Aims:** This prospective study aims (1) to design an image-based VR (IBVR) instruction for clinical medical education, (2) to compare HRV and CL in traditional video-based (VB) learning and novel IBVR-based learning, (3) to compare outcomes of mini-CEX, DOPS, and milestone between two modules, (4) to perform a qualitative evaluation of IBVR-based learning using a 360-degree video review, and (5) to assess various levels of novice learners (undergraduate medical students and postgraduate year residents) for their participation in and acceptance of this novel IBVR-based learning.
   3. **Study Designs:** This 3-year study includes two parts: (1) Design a VR-based curriculum including fundamental otolaryngological skills, and (2) Validation of an IBVR-based history taking and physical examination (H&P) learning activity using a blinded randomized, parallel-controlled trial in convenience-sampled novice undergraduate medical students and postgraduate year residents.
   4. **Materials and Methods:** This study will be implemented between August 1, 2017 and July 31, 2020. Firstly, a VR-based curriculum will be designed including H&P using the analysis, design, development, implementation, and evaluation model and a modified Delphi approach. VB module and IBVR module of the same contexts will be developed. Secondly, an IBVR-based H&P learning activity will be validated by measuring CL questionnaires, reaction time, HRV, mini-CEX, DOPS, milestones, global satisfaction scale and AttrakDiff2 questionnaires (n = 64). Age, sex, and cognitive style (determined by the Group Embedded Figures Test) of both groups are matched. Differences in variables of interests will be statistically analyzed.
2. **Study Design**
   1. **Study Type:** Interventional (Clinical Trial)
   2. **Actual Enrollment:** 64 participants
   3. **Allocation:** Randomized
   4. **Intervention Model:** Parallel Assignment
   5. **Intervention Model Description:** This randomized controlled trial will recruit 64 subjects who are novices in otolaryngology at an academic teaching hospital. The cognitive style of the participants is assessed using the Group Embedded Figures Test. The subjects are randomly assigned (1:1) to a novel image-based virtual reality group and conventional video-based group matched by age, sex, and cognitive style.
   6. **Masking:** Double (Investigator, Outcomes Assessor)

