For the relative small sample size of the present study, we analyzed all variables using non-parametric approaches. The sample size calculations for the trial are performed with G*Power (version 3.1.9.2; University Kiel, Germany) using the primary outcome effects (mean DOPS score; 85±10 [VB module] & 90±10 [IBVR module) in the pilot study. Using a two-tailed Wilcoxon signed-rank test for calculating the sample size (normal parent distribution; effect size, 0.50; type I error, 0.05; power, 95%), we got a sample size of 29 in each group at the minimum power of 0.95. For considering an approximate 10% drop-out rate to fulfill the criteria of intention-to-treat analysis, we needed at least 32 participants to attend this study.

The **inclusion criteria** of the present study are:

1. Age > 20 years old;
2. UME students (defined as the last year of medical school training) and PGY residents (defined as the first year after graduation).

The **exclusion criteria** are:

1. Pregnant, hypertension, recent motion sickness, inner ear infections or claustrophobia, recent surgery, pre-existing binocular vision abnormalities, heart conditions or epileptic symptoms;
2. Declining to participate.

[figure not shown]

1. **GEFT (15 minute):**

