Primary outcome is score of DOPS. Differences in scores of mini-CEX, DOPS, milestones, CLS, TLX, CLL, GSS, PQ, HQ-S, HQ-I, and ATT between IBVR module and VB module are compared using Mann-Whitney *U* test. Changes in reaction time and HRV between IBVR module and VB module are compared using Wilcoxon rank test. Percentage (%) of change ([intervention value – baseline value]/[baseline value] × 100) in reaction time as well as HRV will be calculated and compared with Mann-Whitney *U* test or Wilcoxon rank test as appropriate.

1. **Validation of basic IBVR-based surgical trainings using a randomized, controlled, crossover trial in convenience-sampled novice residents**

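### The 95% power claim rests on a one-sample or matched-pairs test; the planned two-group Mann-Whitney comparison of DOPS has about 45% to 48% power for the stated difference

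*Protocol*

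**What the plan says.** The sample size paragraph (Protocol, 4. Materials and Methods, Participants) takes its inputs from a pilot study: "mean DOPS score; 85±10 [VB module] & 90±10 [IBVR module". It names the test and the settings: "Using a two-tailed Wilcoxon signed-rank test for calculating the sample size (normal parent distribution; effect size, 0.50; type I error, 0.05; power, 95" per cent). The result is given as "we got a sample size of 29 in each group at the minimum power of 0.95". After an allowance of roughly 10% for drop-out, the paragraph ends with "we needed at least 32 participants to attend this study".

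The design and analysis are described elsewhere in the Protocol:

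- Study Design, Intervention Model Description: "This randomized controlled trial will recruit 64 subjects who are novices in otolaryngology", assigned 1:1 in parallel to the two modules.
- Randomization: computer-generated allocation in blocks of 4, intended to balance age, sex and cognitive style.
- Outcome Measurements and Statistics (for the history-taking and physical examination trial): DOPS is the primary outcome, and scores "between IBVR module and VB module are compared using Mann-Whitney *U* test".

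**The concern.** The test used for sizing does not belong to the design. A signed-rank test analyses one set of differences: one sample, or one difference per matched pair. Its effect size is the mean difference divided by the standard deviation of the differences. The protocol enters 0.50, which is (90 − 85)/10, the difference between two groups divided by the standard deviation within a group. A comparison of two independent groups at that effect size needs far more people per arm.

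This calculation is the only justification given for the size of the trial. The protocol also words its null hypotheses as the two modules being equivalent. A reader who trusts 95% power could take a non-significant DOPS result as good evidence that the modules perform alike, when the test would miss the planned 5-point difference about half the time.

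**Working it through.** **Inputs (Protocol, Participants).** Difference 90 − 85 = 5 points; SD 10; effect size 5/10 = 0.50; two-sided alpha 0.05; target power 0.95; normal parent distribution. Group sizes: 29 per group stated; 32 per group if the recruited 64 are split 1:1.

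**Method.** For rank tests with normal data, use the t-test power formula with the sample size multiplied by the asymptotic relative efficiency, 3/π = 0.955.

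**Step 1. The protocol's own figure (signed-rank).** Effective n is m = n × 3/π, noncentrality is 0.50 × √m, and degrees of freedom are m − 1.

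- n = 57: m = 54.4, noncentrality 3.69, critical value 2.01, power 95.2%.
- n = 56: power 94.8%.
- n = 29: m = 27.7, noncentrality 2.63, critical value 2.05, power 71.8%.

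The named test with the stated settings needs 57 pairs (or single observations). The protocol's 29 appears only if 57 is halved: 57/2 = 28.5, rounded up to 29.

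**Step 2. The test the trial will use (Mann-Whitney, two independent arms).** With n per arm, m = n × 3/π, noncentrality is 0.50 × √(m/2), and degrees of freedom are 2m − 2.

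| n per arm | m | Noncentrality | Critical value | Power |
|---|---|---|---|---|
| 29 | 27.7 | 1.86 | 2.01 | 44.7% |
| 32 | 30.6 | 1.95 | 2.00 | 48.5% |
| 67 | | | | 80% |
| 110 | | | | 95.0% |

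Simulation (20,000 trials, normal scores) gave 44.7% at 29 per arm and 47.8% at 32. With scores rounded and capped at 100 it gave 44.7% and 47.5%.

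**Step 3. What the trial can detect (same formula, solved for the effect size; points = effect size × 10).**

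| n per arm | 80% power | 95% power |
|---|---|---|
| 29 | 0.77, or 7.7 points | 0.99, or 9.9 points |
| 32 | 0.73, or 7.3 points | 0.94, or 9.4 points |

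The DOPS scale ends at 100, which strains the larger figures. A 9.4-point shift from 85 puts the mean at 94.4 with SD 10. If such scores are cut off at 100, the difference in observed means is only about 7.9 points.

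**Step 4. Width of the confidence interval.** With SD 10 and 32 per arm, the 95% half-width is about 2.00 × 10 × √(2/32) = 5.0 points.

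**The case against.** The strongest defence is that the groups are described as matched on age, sex and cognitive style, so a paired calculation might be intended. This does not hold. The Randomization section describes balance between groups through blocked allocation. It forms no pairs and states no within-pair correlation, and the planned DOPS test is unpaired. Real pairing would not rescue the claim either. The paired effect size is 0.50/√(2(1 − ρ)), where ρ is the within-pair correlation, which the protocol does not give. With 29 pairs, power is 43% at ρ = 0, 72% at ρ = 0.5 and 94.8% at ρ = 0.75.

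Some limits on the point do stand:

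- **The origin of 29.** A reader might infer that 57 pairs were mistaken for a head-count and halved. That is probable, but the protocol does not say so. A two-group Mann-Whitney calculation at an effect size of 1.0 also gives 29 per arm (power 94.8% at 28, 95.5% at 29), although it contradicts the stated 0.50 and the named test. The conclusion on power does not depend on which happened.
- **What a null result shows.** A reader might infer that a non-significant result can never exclude a 5-point benefit. With a half-width of about 5.0 points, an observed difference between about −5 and 0 is non-significant, yet its interval excludes +5. The interval has to decide.
- **The drop-out step.** One might object that 29/0.9 = 32.2 calls for 33 per group. The allowance is stated only as approximate, and losing 3 of 32 (9.4%) leaves 29, so this is no error.
- **Scope.** Enrolment is recorded as complete at 64. The Mann-Whitney test and its type I error are unaffected.

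**Conclusion.** The stated 95% power is wrong for this design. For the protocol's own 5-point difference with SD 10, the planned Mann-Whitney comparison has about 45% power with 29 analysed per arm and about 48% if all 32 per arm are analysed. The type II error is therefore roughly 52% to 55%, against the 5% implied. Power of 95% would take about 110 per arm.

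These figures assume normal scores with equal SDs of 10, two-sided 0.05 and independent arms. Capping scores at 100 hardly changes the power at 5 points, but it makes the larger detectable differences approximate. The error lies in the stated power and in how a null result may be read. The documents do not support reading it as a flaw in the randomisation or in the primary test itself.

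**What to change.** Keep 64 participants and rewrite the sample size paragraph:

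1. Replace the signed-rank calculation with a two-group Wilcoxon-Mann-Whitney one on the same inputs.
2. State power of about 45% for a 5-point difference with 29 analysed per arm after 10% drop-out, and about 48% if all 32 per arm are analysed.
3. State detectable differences of about 7.7 points (80% power) and 9.9 points (95% power) with 29 per arm, or 7.3 and 9.4 with 32 per arm. Note that these use a normal approximation which the 100-point ceiling strains for the larger differences.
4. Correct the closing figure to 32 per group (64 in total), in line with the 64 given elsewhere in the Protocol.
5. Report the DOPS difference with its 95% confidence interval and judge from that interval whether a 5-point difference is excluded, so that a non-significant test is not read as equivalence.

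The cost is protocol wording and one added interval in the report. No participants are added and the primary test stays the same. The stated power becomes much less favourable.

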**4. Materials and Methods**

1. **Study Proposal and Reasons:**
2. **Study design**

Originally, this ***3-year study*** includes three parts: (1) Design a VR-based curriculum including fundamental otolaryngological skills such as H&P and basic surgeries; (2) Validation of an IBVR-based H&P learning activity using a blinded randomized, parallel-controlled trial in convenience-sampled novice UME and PGY learners; and (3) Validation of basic IBVR-based surgical trainings using a randomized, controlled, crossover trial in convenience-sampled novice residents. The present study will be conducting from August 1, 2017 to July 31, 2020 at a tertiary medical center–Linkou Chang Gung Memorial Hospital, Taoyuan, Taiwan. This study is approval by the Institutional Review Board of Chang Gung Medical Foundation, Taipei, Taiwan. All procedures will be carried out in accordance with the current regulations. All of the subjects need to provide written informed consent to participate in this study. With this research, something out of the ordinary is being done in their community. It is possible that if others in the community are aware that they are participating, they may ask them questions. We will not be sharing the identity of those participating in the research. The information that we collect from this research project will be kept confidential. Information about the subjects that will be collected during the research will be put away and no-one but the researchers will be able to see it. Any information about the participants will have a number on it instead of their name. Only the researchers will know what their number is and we will lock that information up with a lock and key. It will not be shared with or given to anyone except research sponsors or DSMB board.

1. **Design an IBVR-based curriculum including fundamental otolaryngological skills such as H&P and basic surgeries**

Since the recommended duration of IBVR is within 15 minutes, we choose 5 representative teaching activities that can complete in 15 minutes: H&P, ventilation tube insertion, preparation of navigation-assisted endoscopic sinus surgery, preparation of microscopic laryngeal surgery, and tracheostomy.

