We plan to recruit 64 volunteers from 70 UME participants who have listened our initial instruction of the present study and completed a 15-minute GEFT (3-minute illustration and 12-minute test). The GEFT test which is the most widely used version of pencil-and-paper tests in FD/FI investigations.^54^ The GEFT is a 25-item test that requires participants to locate and trace simple geometric figures embedded within progressively more complex ones. This test has three sections and the procedures for the administration of GEFT strictly follow the directions included in the manual (GEFT booklet pack, Mind Garden, Inc., Menlo Park, CA, USA). The first section is a practice section that contains seven simple embedded figures, and it is not scored. The time limit on this section is two minutes. The real task begins at the second set and into the third one, where the participants have to find the simple geometric figures inside two 9-itemed set within the time limit of five minutes for each of the booklet. Based on the number of correct answers given by subjects, the scores on GEFT range from 0 (the most FD) to 18 (the most FI). Those who intend to rely on external cues are less able to find the simple figures (FD), and those who hinge on internal cues are abler to find figures (FI). In this study, we will apply an English version of the GEFT that GEFT scores ≤12 are considered as ‘FD’ and those with GEFT scores >12 are regarded as ‘FI’.

1. **Randomization:**

The randomization procedure assures balanced design in age, gender, and FD/FI. Computer-generated lists of random numbers are created using Random Number Generators of SPSS software for allocation of the participants and are stratified by center with a 1:1 allocation using a fixed block size of 4 (Rv. Uniform [0, 1]) in both subgroups. The allocation sequence is concealed from the blinded researcher before instruction adhering to our computer-generated randomization protocol. Participants are randomly allocated to either IM or PPS group. Half of the patients are randomized to the IBVR group and the remaining patients are randomized to the VB group. This protocol follows the rules of the CONORT 2010.^58^

1. **Learning Material Provided (10 minutes):**

The VR-based learning is a computer program that will be developed at the Linkou-Chang Gung Memorial Hospital and Chang Gung University and. VB-based learning materials can be linked to the

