2. We may need more eligible candidates as anticipated since we want to control age, gender, and FD/FI ratios. Fortunately, there are approximate 100 UME and PGY students from various medical colleges to be trained in our Teaching Clinics each year. Moreover, participants may withdraw from the trial or become "lost to follow-up" in most longitudinal studies of human subjects. According to our previous experience, we extremely need an experienced research assistant (RA) to recruit subjects, obtain written inform consent forms, performing experiments, and manage our experimental data. The best resolution is the MOST agree us to hide a RA in this three-year study.
3. Such as mentioned above, missing-data will be a big problem in this longitudinal study. In additional to a full-time RA, we can use an optimal method such as GEE approach to analyze the data according to the principle of the intention to treat.
4. Despite we have some experience in instructional design of mobile e-learning (M-TEL), VR is still a tremendous challenge to us because of complex program and hardware technologies and expensive instruments. Due to limited resource, we construct an experienced team including experts of medical education.
5. **Anticipated Outcomes:**
   1. **Anticipated progression of the study**

We will conduct the three-year study between August 1, 2017 and July 30, 2020. In the first year, we plan to design a VR-based curriculum including H&P and parts of basic surgeries with verification in a pilot study and validate an IBVR-based H&P learning activity using a blinded randomized, parallel-controlled trial in convenience-sampled novice UME and PGY learners (*n* = 24). In the second year, we will complete the design work of a VR-based surgical trainings with verification in a pilot study and finish the validation of an IBVR-based H&P learning activity using a randomized controlled trial (*n* = 40), and begin to recruit 10 junior residents to validate a basic IBVR-based surgical trainings using a randomized, controlled, crossover trial in convenience-sampled novice residents. In the third year, we will complete the validation of IBVR-based surgical trainings using a randomized crossover trial, and data analysis and manuscript preparation.

- 1. **Anticipated contributions to academic research, national development, and other clinical applications**

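### The randomisation paragraph promises balance on age, sex and field dependence, but the only stratification factor it names is centre, in a one-centre trial

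*Protocol*

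**What the plan says.** The Randomization paragraph for the history-and-physical (H&P) trial (Protocol, section 4) opens with a guarantee: "The randomization procedure assures balanced design in age, gender, and FD/FI". The Intervention Model Description under Study Design presents the two arms as "matched by age, sex, and cognitive style". The account of the H&P validation trial in section 4 likewise says that allocation is controlled for these three factors.

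The mechanism is one sentence. The computer-generated lists "are stratified by center with a 1:1 allocation using a fixed block size of 4 (Rv. Uniform [0, 1]) in both subgroups". Centre is the only factor named, and the two subgroups are not identified there or elsewhere. The Study design paragraph places the work "at a tertiary medical center–Linkou Chang Gung Memorial Hospital, Taoyuan, Taiwan", and the Locations entry lists that hospital alone.

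Eligibility covers final-year undergraduates (UME) and first-year postgraduates (PGY). The GEFT paragraph, however, says "We plan to recruit 64 volunteers from 70 UME participants".

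**The concern.** Balance guaranteed by design and balance expected on average are different properties. A reader told that the arms are matched will discount age, sex and cognitive style as explanations for a difference. The procedure as written gives no basis for that on at least two of the three factors.

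The analysis does not close the gap. The primary outcome, DOPS, is compared by an unadjusted Mann-Whitney test (Outcome Measurements and Statistics). The two-way ANOVAs under Statistical Analysis pair the module with sex or with FD/FI, one factor at a time, and never include age or training level.

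The sponsor has reason to care about cognitive style. In its earlier data (Introduction, Virtual Reality), FD and FI learners differed on a multimedia situational test (-20% ± 20% against 16% ± 27%, P = 0.040) and on satisfaction with game-based learning (P = 0.011).

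**Working it through.** **Inputs.** 64 participants, 1:1, fixed blocks of 4 (Study Design; Randomization). One centre (Study design; Locations). FD share 13% (Introduction, Virtual Reality). Shares of women and of PGY learners are not given and are assumed below.

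**1. The plan's own totals.** 64 / 4 = 16 complete blocks, each 2:2, giving 32:32. With one list, the stated 1:1 allocation is reproduced. This balance in totals is all that one-centre blocking secures.

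**2. What each reading of the subgroup phrase would balance by design.**

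| Reading | FD/FI | Sex | Age | Training level |
|---|---|---|---|---|
| FD and FI | yes | no | no | no |
| UME and PGY | no | no | no | yes |
| No stratum (for example, the two arms) | no | no | no | no |

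No row covers all three promised factors.

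**3. Size for FD/FI if it is not a stratum.** Expected FD learners: 0.13 × 64 = 8.3, so 8 or 9. With 8, the number in one arm is hypergeometric: P(k) = C(32,k) × C(32,8−k) / C(64,8), where C(64,8) = 4,426,165,368.

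- k = 2: 496 × 906,192 = 449,471,232
- k = 1: 32 × 3,365,856 = 107,707,392
- k = 0: 10,518,300
- Sum 567,696,924; doubled for both arms 1,135,393,848; divided by C(64,8) = 0.257

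So a split of 6:2 or worse has probability about 26%, and 7:1 or worse 5.3%. Simulating 100,000 lists of 16 blocks of 4 gave 25.8% and 5.3%. With 9 FD learners, 6:3 or worse has probability 47% and 7:2 or worse 15%.

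If FD/FI is a real stratum with blocks of 4, the arms cannot differ by more than 2 FD learners, and 8 FD learners split exactly 4:4.

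**4. Sex and training level if not strata (assumed shares).** With 32 of 64 in a category, a difference of 6 or more between arms (19:13 or worse) has probability 21%. With 20 of 64 (13:7 or worse) it is 18%.

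**5. Possible effect on DOPS.** The FD/FI effect on DOPS is not given. Assuming 5 to 15 points, a 6:2 split moves the arm difference by (6/32 − 2/32) × 5 to 15 = 0.6 to 1.9 points, against the planned difference of 90 − 85 = 5.

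**6. Predictability of fixed blocks of 4.** The fourth allocation is always determined by the first three. The third is determined when the first two agree, which has probability 1/3. That is (1 + 1/3) / 4 = 1/3 of allocations, about 21 of 64. The best guess is right (1/2 + 2/3 + 2/3 + 1) / 4 = 71% of the time. Both figures require someone who sees earlier allocations and knows the block boundaries.

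**7. Signs of carried-over text.** The same paragraph assigns participants to groups labelled IM and PPS, which are not arms of this trial. The crossover part, whose residents come from three hospitals, also stratifies by centre, where it could have a purpose.

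**The case against.** The strongest reply is that the subgroup phrase does real work. It and the block size are absent from the parallel paragraph for the crossover part, so both look specific to this trial. FD/FI is the dichotomy defined just before it, and UME/PGY are the trial's two populations. On the first reading the 26% disappears; on the second, training level is balanced. This stands: neither the 26% nor the omission of training level can be asserted without condition. It does not rescue the claim, because neither reading covers age and sex.

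Control may also come from elsewhere. The section on anticipated problems says more candidates may be needed so that age, gender and FD/FI ratios can be controlled, and the ANOVAs bring in sex and FD/FI. But no recruitment rule that would achieve this is described, and the ANOVAs are not a joint adjustment.

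A reader might infer that allocations were foreseen, since the sponsor writes "we extremely need an experienced research assistant (RA) to recruit subjects, obtain written inform consent forms, performing experiments, and manage our experimental data". The protocol does not support that. It is a staffing request, nothing says the assistant sees past allocations, and the Randomization paragraph claims concealment, though without a mechanism. With 64 of 70 candidates to be enrolled, there was also little room for selection. Varied block sizes are therefore a secondary safeguard here.

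The evidence that cognitive style matters is mixed: the multiple-choice test (P = 0.303) and the global satisfaction scale (P = 0.097) did not differ significantly. No figure links training level to DOPS.

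**Conclusion.** The point holds as a mismatch between claim and mechanism. The protocol asserts balance and matching on age, sex and FD/FI, and no reading of its procedure delivers all three. Age and sex are uncontrolled by design on every reading; FD/FI and training level depend on an undefined phrase.

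The size is conditional. If FD/FI is not a stratum and about 8 of 64 are FD, a split of 6:2 or worse has probability about 26%. On an assumed FD/FI effect of 5 to 15 DOPS points, such a split would move the comparison by up to about 2 points.

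A reader might go further and infer that the randomisation is invalid or the DOPS comparison biased. The document does not support this: 1:1 allocation without these strata is valid, and chance imbalance favours neither arm in expectation. What is unsupported is the assurance.

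The recruitment sentence is a separate inconsistency. If all 64 really were UME students, training level would drop out of this point, but eligibility and the fifth aim would then be wrong.

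**What to change.** **If allocation could still be changed.** State what the two subgroups are. Replace centre with FD/FI, sex and training level, all known before allocation (GEFT is completed first). Minimisation with a random element suits 64 participants better than fully crossed strata: crossing FD/FI with sex and two assumed age bands leaves about 0.13 × 64 / 4 = 2 learners per FD cell, and about 1 once training level is added, less than one block. Either add an age band or drop the claim on age. If blocks are kept, vary their size and do not disclose it. The cost is a new list or allocation script, with no extra participants or visits.

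**If allocation is done.** The Study Design section reports enrolment of 64 and completion in October 2020 as actual, so this is the practical route. Define the subgroups as they were used, and delete the wording that assures balance and calls the arms matched. Alongside the Mann-Whitney test, add a DOPS comparison adjusted jointly for FD/FI, sex, age and training level, labelled as added later if results have been seen. The cost is one further model on data already collected.

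**In either case.** Reconcile the sentence recruiting 64 from 70 UME participants with the UME and PGY eligibility criteria, and correct the IM and PPS group labels.

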Expectedly, virtual environment users often report having a sense of being present in the virtual place or a sense that the virtual object is present in their environment. This sense of presence depends on both the technological fidelity (e.g., in graphics, haptics) and the users' cognitive/ personality characteristics. Hecht and Reiner found that field-independent (FI) individuals reported higher presence ratings compared to field-dependent participants.^15^ Field dependency is defined as the degree to which a person’s perception is affected by the context of the surrounding perceptual field.^16^ The field-dependent (FD) individuals perform poorly on the Rod & Frame test, as they take the frame as a reference point for horizontal and vertical and try to rotate the rod in relation to the frame. In our recent studies that supported by the Ministry of Science and Technology (104-2511-S-182 -010 - & 105-2511-S-182A-006 -), we preliminarily found 13% of UME students were FD and 87% were FI. Although mean change of duplicated multiple choice questionnaire (MCQ) was equivalent (155% ± 126% vs. 56% ± 54%, *P* = 0.303) between FD group and FI group and mean change of duplicated multimedia situational test (MST, duplicated) of the FD group was significantly lower than that of the FI group (-20% ± 20% vs.16% ± 27%, *P* = 0.040) after a 100-minute M-TEL instructional course of emergent otorhinolaryngology-head and neck disorders. Nevertheless, global satisfaction scale (GSS) reported by FD subjects was not statistically significantly lower than that of FI subjects (5.0 ± 2.6 vs. 7.3 ± 2.1, *P* = 0.097). FI learners reported a significantly higher satisfactory to game-based learning (GBL) (8.5 ± 0.5 vs. 6.1 ± 2.4, *P* = 0.011). These findings suggested that more than 80% of UME students are FI and can perform M-TEL well, especially preferred to use the GBL module well. In contrast, as Hecht and Reiner’s findings,^15^ there was a possible linkage between FD, the sense of presence, and simulator sickness phenomenon. However, their knowledge gaining seemed not to be reduced in terms of MCQ test. Despite cognitive style can refer to the individual’s consistent attitudes for perceiving, remembering, organizing, processing, thinking, and problem solving in e-learning programs,^17^ it seemed not significantly affect UME students’ preference to use e-Learning, but the youngth generation (Y-generation) obviously liked to use the GBL module of M-TEL. When we used the AttrakDiff2 questionnaire,^18^ to be able to quantify attractive, identifiable, stimulating, and pragmatic qualities according to their learning experience, UME students felt more attractive to the M-TEL (attractive score ≥ 1.5) had a better MCQ score than those felt less attractive (< 1.5; 103% ± 84% vs. 42% ± 50%, *P* = 0.039). These findings could be explained by reduced cognitive load (CL). Two ‘FD’ students in our previously studies reported that ‘GBL confused their directions of learning and they needed very, very high intensity of mental effort to pass the games in order to learn the instructional content’. The group interview suggested the importance of cognitive style and CL overload in M-TEL.

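### The primary DOPS test is an unadjusted Mann-Whitney U although the protocol says the arms are balanced on age, sex and cognitive style; a model including these factors would probably recover some power

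*Protocol*

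**What the plan says.** For the history-taking and examination trial, the protocol's Outcome Measurements and Statistics section states "Primary outcome is score of DOPS". It puts DOPS in a list of scores tested in one way; the list ends "HQ-S, HQ-I, and ATT between IBVR module and VB module are compared using Mann-Whitney". No covariate or stratum is named. The Participants section gives the general policy and its reason, a relatively small sample: "we analyzed all variables using non-parametric approaches".

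On allocation, the Intervention Model Description speaks of a "conventional video-based group matched by age, sex, and cognitive style". The trial description and the Randomization section say much the same, and every participant takes the Group Embedded Figures Test (GEFT), which classifies them as field-dependent (FD) or field-independent (FI). The only stratifier that the Randomization section names is center, with blocks of four in two subgroups that it does not define.

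The Statistical Analysis section adds two-way ANOVAs of learning outcomes on module together with sex, and on module together with FD/FI. They take one factor at a time, leave out age, and are not called the primary analysis.

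**The concern.** A design that balances arms on factors thought to matter is normally analysed with those factors in the model. If the factors predict the outcome and the arms are balanced on them, an unadjusted test measures the arm difference against a variance that still contains the between-factor spread. The test is then conservative and loses power. If the balance is not achieved, which is possible given the mechanism described, chance differences in the factors stay in the arm comparison.

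This matters more here than usual because the trial is short of power at its own assumed effect. In addition, two unranked analyses of the same outcome (a Mann-Whitney P value and a module effect from a two-way ANOVA) leave room to choose between them afterwards.

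**Working it through.** **Inputs from the protocol (Participants section).** Means and SD: "mean DOPS score; 85±10 [VB module] & 90±10 [IBVR module", so d = (90 − 85)/10 = 0.50. Other settings: "normal parent distribution; effect size, 0.50; type I error, 0.05; power, 95". Enrolment is 64, that is 32 per arm. The R² of age, sex and FD/FI for DOPS is not given; I assume 0 to 0.3.

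**The plan's own figure.** The sizing reads "Using a two-tailed Wilcoxon signed-rank test for calculating the sample size" and arrives at 29 per group. For a rank test with a normal parent distribution, multiply n by the relative efficiency 3/π and use the noncentral t distribution.
- Signed-rank (one sample or pairs), n = 57: noncentrality = 0.5 × √(57 × 3/π) = 3.69, power 0.952. Half of 57, rounded up, is 29. The stated figure is therefore reproduced as the total for a paired test, split over two arms.
- Planned two-arm test, 32 per arm: effective n per arm = 32 × 3/π = 30.56; noncentrality = 0.5 × √(30.56/2) = 1.954; power 0.485. With 29 per arm it is 0.447. Reaching 0.95 would need 110 per arm.

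**Effect of adjustment, 32 per arm.** Replace d by d/√(1 − R²) and take 64 − 2 − 3 = 59 degrees of freedom for three covariates. Example at R² = 0.2: d = 0.5/√0.8 = 0.559. For rank ANCOVA the noncentrality is 0.559 × √(30.56/2) = 2.185, power 0.575. For linear ANCOVA it is 0.559 × √(32/2) = 2.236, power 0.595.

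| Assumed R² | Mann-Whitney U | Rank ANCOVA | Linear ANCOVA |
|---|---|---|---|
| 0 | 0.485 | 0.485 | 0.503 |
| 0.1 | 0.485 | 0.527 | 0.545 |
| 0.2 | 0.485 | 0.575 | 0.595 |
| 0.3 | 0.485 | 0.632 | 0.652 |

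The like-for-like comparison is Mann-Whitney U against rank ANCOVA. About 2 points of the linear model's advantage come from leaving ranks (0.503 at R² = 0), not from adjusting.

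**Simulation check (4,000 runs per setting, 32 per arm).**
- Arms balanced on all three factors: the unadjusted test's type I error was 0.046 at R² = 0, 0.029 at 0.2 and 0.020 at 0.3. Rank ANCOVA stayed between 0.044 and 0.054. At R² = 0.2, power was 0.47 unadjusted, 0.57 with rank ANCOVA and 0.59 with linear ANCOVA.
- Allocation not balanced on the factors: the unadjusted test's type I error was 0.045 at R² = 0.2 and 0.047 at 0.3, so it is valid. Power at R² = 0.2 was 0.48 unadjusted and 0.56 with rank ANCOVA.
- Rounding DOPS and capping it at 100 left the pattern unchanged (R² = 0.2: 0.47, 0.56 and 0.57).

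**Is there an anchor for R²?** Not a usable one. The Virtual Reality section reports that the mean change on the "multimedia situational test (MST, duplicated) of the FD group was significantly lower than that of the FI group" in an earlier course (−20% ± 20% against 16% ± 27%, P = 0.040), with 13% of students FD. The gap is 36/√(0.13 × 20² + 0.87 × 27²) = 36/26.2 = 1.37 SD. Then R² = 0.13 × 0.87 × 1.37²/(1 + 0.13 × 0.87 × 1.37²) = 0.18. But this is percentage change on a different test. On the multiple-choice test the same section gives a difference in the opposite direction (155% against 56%, P = 0.303), and overall satisfaction did not differ significantly (P = 0.097).

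**The case against.** The strongest reply is that nothing here is invalid. Ignoring balanced factors makes the Mann-Whitney U conservative, and chance imbalance does not undermine a randomised comparison. The protocol gives a reason for rank methods, and DOPS is capped at 100 with an assumed mean of 90 ± 10 in one arm. All of that stands, and it is why rank ANCOVA fits the plan at least as well as a linear model.

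Second, the factors are not ignored altogether: the planned two-way ANOVA with FD/FI yields a module effect adjusted for FD/FI. That also stands, but it covers one factor at a time, never age, and is not the primary test.

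Third, the gain may be small. Eligibility is limited to final-year students and first-year residents, so age probably varies little, and at 13% only about 8 of 64 participants would be FD (0.13 × 64 = 8.3). This is correct, and it is why the range starts at no gain.

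A reader might infer that the choice of test is what leaves the trial near 48% power, or that adjustment would rescue it. The documents support neither. The shortfall comes from the signed-rank sizing, and 80% power at 32 per arm would need R² of about 0.51 with linear ANCOVA (0.55 with rank ANCOVA). A reader might also take the earlier FD/FI data to show that cognitive style explains nearly a fifth of DOPS variance. Those data concern other outcomes and are mixed.

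Finally, an unseen SAP may add adjusted models and interval estimates, so their absence from the protocol is not a fault. The primary test, however, is fixed in the protocol.

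**Conclusion.** The point holds as a modest, nearly free improvement. The primary DOPS test leaves out factors that the protocol collects and says it balances. It is valid but probably forgoes some power: nothing at R² = 0, about 4 points at 0.1, 9 at 0.2 and 15 at 0.3 when rank methods are compared like for like. These sizes rest on d = 0.5, 32 analysed per arm, near-normal scores and an R² that is assumed. The conservatism also depends on the balance being achieved; the protocol asserts this, but center is the only stratifier it names. Without that balance, adjustment still helps by removing chance imbalance from the comparison. None of this repairs the sample size, which has to be recalculated separately for two independent arms.

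**What to change.** In Outcome Measurements and Statistics, name one prespecified primary analysis of DOPS: a model with arm, GEFT score (or FD/FI), sex and age. Add learner level if both students and residents are enrolled; eligibility admits both, but the GEFT section describes recruiting the 64 from 70 undergraduates. Use rank ANCOVA to keep the stated non-parametric approach, or a linear model if an adjusted mean difference with 95% CI is wanted. Keep the unadjusted Mann-Whitney U as a sensitivity analysis, and label the two-way ANOVAs as supportive. The other scores can follow the same pattern.

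Cost: one or two sentences and no new data. Three covariates leave 59 of the 62 degrees of freedom, four leave 58. If the factors do not predict DOPS there is no gain, and the loss is negligible (power 0.485 with or without adjustment at R² = 0).
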